### Interventions

The randomly allocated study interventions may differ for centres across countries. While in Colombia EQUITY will offer masked (i.e. similar-looking) treatments, including placebo or active treatments, in the remaining centres it will be a pragmatic, open-label trial, where the control group may not receive medication (see further explanation in the following paragraphs).

In Colombian centres, before randomisation, in order to ensure adherence to study interventions, eligible, consenting individuals will go over a 10-day, run-in treatment (with placebo). This treatment placebo, blinded for participants, has a similar appearance to the study drug and will be given in similar fashion (2 capsules twice a day [BID]). Those reporting tolerance and adherence (not experiencing symptoms judged as moderate/severe and taking at least 80% of the capsules) will be prescribed a blinded treatment of 2 capsules BID for 120 days. This includes a sequence-concealed, randomly allocated treatment with any of the following five treatment groups (ratio 1:1:1:1:1):NFX 480 mg/day for 60 daysNFX 240 mg/day for 120 daysBZN 300 mg/day for 60 daysBZN 150 mg/day for 120 daysPlacebo

Two of the four groups with active treatment will have a 60-day, conventional dose (60CD) of either NFX or BZN, whereas the other two groups include 120-day, half-dose (120HD) treatment. As the prescribed study treatment for all groups takes 120 days, the 60CD groups will receive another 60-day masked placebo treatment that precedes or follows the active treatment in a randomly assigned sequence. Figure 1 summarises the study arms and assigned treatments. To ensure the blinding to participants and their relatives, treating physicians and study teams, the study medication will be packaged in a similar fashion. We used similar gelatin capsules to include and mask the contents of the original tablets of active treatments or placebo (a mix of microcrystalline cellulose and magnesium stearate), as shown in Fig. 2. The study medication was packed in bottles of 120 capsules (intended to last for 2 months) labelled with the study name and treatment codes, making the study arms indistinguishable from each other.

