### Outcomes

#### Efficacy

The primary outcome will be the proportion of participants testing positive at least once for up to three independent assays of polymerase chain reaction (PCR) during the 12–18 months after the initiation of treatment, with an interval of 7 or more days from each other. Secondary efficacy outcomes will be (1) the mean change in the levels of B-type natriuretic peptides (either NT pro-BNP or BNP, as long as the same test is used for each participant) and (2) the proportion of participants with positive serological status (using conventional serology diagnosis) 12 months after the initiation of treatment. Centres outside Colombia may or may not, depending on the resources available and practice patterns, provide data on BNP or conventional serology after treatment. All efficacy outcomes will be recorded and analysed without knowledge of treatment allocation.

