### Statistical analysis

Reporting of trial results will include a description of the enrolment process and the most relevant characteristics of the participants. For this purpose we will use counts and proportions or means and standard deviations for discrete and continuous variables, respectively.

Our outcome measures will be discrete variables, with the exemption of mean changes in the BNP levels, a secondary outcome for efficacy. For the purpose of evaluating the efficacy of NFX over placebo, we will test a hypothesis of no difference in the proportions of 1 + PCR at an alpha level of 1%. For the purpose of testing the equivalence of NFX to BZN or between 60CD and 120HD regimes, we will run a one-tailed non-inferiority test at an alpha level of 1%. In order to test for agent-dose interaction for the above comparisons, we will construct logistic regression models with the primary outcome as the event, and the comparison groups and study arms (e.g. NFX 60CD or NFX 120HD) as predictor variables. We will include the interaction dose*agent term in the model and run this test for no differences at an alpha level of 5%.

For the purpose of evaluating mean changes of BNP among groups, we will test for differences using independent-sample Student’s *t* tests comparing the groups of interest (alpha level of 1%). For the dose-agent interaction test (alpha level 5%), we will run an analysis of covariance with the mean changes as response, the comparison and study arms as factors and the interaction term.

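### BNP change is compared without its baseline value as a covariate, and the agent-dose interaction model, read literally, leaves the interaction no degrees of freedom

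*Protocol article*

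**What the plan says.** All references are to the protocol article.

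**BNP outcome.** The Efficacy section makes the mean change in natriuretic peptide level a secondary outcome. The assay may be "either NT pro-BNP or BNP, as long as the same test is used for each participant". BNP data are optional outside Colombia. Laboratory testing says that efficacy samples are stored and processed centrally in reference laboratories, but it does not say which of the two peptides will be measured.

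**BNP analysis.** Statistical analysis compares mean changes by independent-sample Student's t tests at 1%. The dose-agent interaction is tested at 5% by "an analysis of covariance with the mean changes as response, the comparison and study arms as factors and the interaction term". No covariate is named.

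**Primary-outcome interaction.** The purpose is stated as "In order to test for agent-dose interaction for the above comparisons". The comparisons listed just before include NFX against placebo. The logistic model takes "the comparison groups and study arms (e.g. NFX 60CD or NFX 120HD) as predictor variables", and the text continues: "We will include the interaction dose*agent term in the model and run this test for no differences at an alpha level of 5" per cent.

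**Arms.** Colombian participants are allocated to "any of the following five treatment groups (ratio 1:1:1:1:1"). As Interventions puts it, "Two of the four groups with active treatment will have a 60-day, conventional dose (60CD) of either NFX or BZN", and the other two active groups receive the 120HD regimen. The active arms are therefore a complete 2x2 of agent by regimen, with placebo alongside.

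**The concern.** There are two specification faults.

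The first is in the BNP analysis. A t test on change subtracts the baseline with a fixed coefficient of 1 and ignores how strongly baseline actually predicts follow-up. Regression on baseline uses the same data and is more precise. The label analysis of covariance suggests that this was intended, but the listed terms make the model an analysis of variance on change. Two different analytes may also enter one mean change with no stated rule for combining them, so the unit of the result and the weight each participant carries are unclear.

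The second is in both interaction models. The protocol's own example of an arm (NFX 60CD) names both an agent and a regimen. Once such arms are in the model they use up all the variation between groups, and a dose*agent term has nothing left to explain. What the software then prints depends on which redundant column it drops. The Abstract lists the agent-dose interaction among the main comparisons, so its result should not depend on coding chosen at analysis.

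**Working it through.** The plan gives no figure for this point to reproduce. The checks are a variance formula and counts of model columns against rank.

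**1. Baseline adjustment for BNP**

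Input: the correlation r between baseline and follow-up. The documents do not give it, so a range is assumed.

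Let the baseline and follow-up SDs be s1 and s2.
- Variance of the change: s1² + s2² − 2·r·s1·s2
- Residual variance after regression on baseline: s2²(1 − r²)
- Difference: (s1 − r·s2)², which is never negative. In large samples adjustment cannot lose.

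With equal SDs, the ratio of adjusted to change-score variance is (1 − r²) / [2(1 − r)] = (1 + r)/2.

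| assumed r | variance ratio | reduction | 60 adjusted equal, unadjusted |
|---|---|---|---|
| 0.5 | 0.75 | 25% | 60/0.75 = 80 |
| 0.7 | 0.85 | 15% | 60/0.85 = 71 |
| 0.8 | 0.90 | 10% | 60/0.90 = 67 |
| 0.9 | 0.95 | 5% | 60/0.95 = 63 |

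The 60 is the Colombian target per group in Sample size calculations and serves only to give the scale.

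**2. Two assays in one mean change**

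The documents give no SDs. Suppose a share p of participants have an assay whose change has k times the SD of the other. Their share of the pooled within-group variance is p·k² / [(1 − p) + p·k²]. With p = 0.2:
- k = 2: 0.8/1.6 = 50%
- k = 5: 5/5.8 = 86%
- k = 10: 20/20.8 = 96%

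This shows what could happen if unscaled values were pooled. It does not predict that they will be.

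**3. Interaction model, four active arms**

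Four groups support at most four independent parameters: the intercept and 3 df.
- Literal model (intercept, agent, three arm indicators, agent*dose): 6 columns, rank 4. Without agent*dose the rank is still 4, so the interaction has 4 − 4 = 0 df.
- With a dose main effect added: 7 columns, rank 4, and the interaction again has 0 df.
- Agent + regimen + agent*regimen, without arm: 4 columns, rank 4. Without the interaction the rank is 3, so it has 1 df.

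A logistic fit to simulated data (60 per active arm, assumed positive proportions 30%, 25%, 45% and 50%) agreed. Adding agent*dose to the arm model changed the deviance by 0 on 0 df. The 2x2 model gave a 1-df test and the same fitted values as the arm model. The BNP interaction model lists the same terms, so the same count applies.

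**4. NFX versus placebo**

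There are three groups: placebo, NFX 60CD and NFX 120HD. With columns intercept, agent, dose and agent*dose, the rows are (1,0,0,0), (1,1,0,0) and (1,1,1,1). The dose and agent*dose columns are identical, giving 4 columns and rank 3. Placebo has no dose level, so there is no agent-dose interaction to test even with arm removed. With all five arms and the literal terms, the count is 9 columns and rank 5.

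**The case against.** The strongest reply is that this is loose wording in a condensed article. The example of arms holds the agent fixed and varies the regimen, so arm could mean regimen within agent. That reading is full rank (4 columns, rank 4) with a 1-df interaction. An analyst who met a rank warning would probably arrive there, with the same fitted values. This largely stands for the active arms. It does not rescue the NFX-placebo comparison, and it sits uneasily with an example in which each arm names both agent and regimen.

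On BNP, the reply is that a t test on change is valid in a randomised trial, that the outcome is secondary, and that an article may leave the covariate's name to the analysis plan. Validity is conceded. But the unadjusted t test is stated as the main analysis; it is not left open.

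A reader might also infer four stronger things, none of which the documents support:
- *That the trial cannot estimate the interaction.* It can. Only the literal coding fails.
- *That the pooled NFX-BZN and 60CD-120HD comparisons depend on the interaction test.* The Comparisons section says the interactions will also be tested. It does not make the pooled comparisons conditional on them.
- *That two assays will be averaged on the raw scale.* The article allows the assay to differ between participants but states neither a scale nor a combining rule. Central processing may lead to one assay, and BNP is optional outside Colombia.
- *That treatment comparisons on BNP are biased.* Randomisation is stratified by centre, so an assay that varies by centre would not systematically favour an arm. The harm is an unclear unit and unequal weighting.

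**Conclusion.** The point holds as a matter of precision and clear specification. The unadjusted BNP analysis forgoes a variance reduction of 10% to 25% over assumed correlations of 0.8 to 0.5, and 5% at 0.9, taking equal SDs at the two times. No bias follows. The rule on assays leaves open how two analytes would combine; the size of that problem cannot be judged from the documents. The interaction model as literally written gives 0 df for dose*agent in both the logistic and the BNP analysis, and the term does not exist for NFX versus placebo under any coding. The underlying 1-df contrast is available from the four active arms. The tests of the primary PCR comparisons and the sample size are unaffected.

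**What to change.** **BNP.** Replace the t tests and the factor-only model by a regression of follow-up BNP, preferably on the log scale, on baseline value (same scale), treatment, centre and the randomisation strata. Use it for the main and the interaction comparisons. On the log scale, report the ratio of geometric means.

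**Assay.** Use one assay in the central processing. If both must stay, analyse on the log scale with assay as a stratum and a separate baseline term for each assay. State that pooling fold changes assumes similar proportional treatment effects on the two analytes, which nothing in the article establishes.

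**Interaction.** Write the model as agent + regimen + agent*regimen within the four active arms, without arm, with centre and strata. Test the single interaction coefficient at the stated 5%. Drop the agent-dose interaction for NFX versus placebo.

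**Cost.** Wording in the analysis plan, and a laboratory decision if one assay is chosen. No additional participants or visits are needed, because the change outcome already requires baseline BNP. The wording should be settled before unblinding, so that neither the coding nor the scale is chosen after results are seen.

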## Discussion

Closing gaps in clinical research is critical for a field like Chagas disease, where major initiatives focused over the last decades on vector control to interrupt transmission [18, 19]. Most with relatively little data, particularly trials on trypanocidal treatment, have originated in Brazil and Argentina. More recently, there have been trials originating outside Latin America (e.g. in Spain and Canada). In the landscape of research on trypanocidal therapy, the EQUITY trial will tackle an important question on therapy for *T. cruzi* infection. As both NFX and BZN are currently used under recommendations and distribution of health authorities, this may be seen as a phase IV study. However, by expanding and validating the information on the effects of NFX, the study has the potential to challenge current recommendations on using alternatively NFX or BZN as similar interventions. In particular, this trial may benefit its target population from countries with fewer or no data from previous trials, or those where the best evidence indicates that BZN lacks a trypanocidal effect. Colombia, the country originating this trial, fits this situation. EQUITY thus represents a step forward for Colombia in terms of conducting this investigator-initiated, publicly funded trial for this largely neglected disease [20].

EQUITY will provide data and insight on three important aspects regarding the use of the two recognised possibilities for trypanocidal therapy, BZN and NFX. While testing the efficacy of NFX as a trypanocidal agent and the equivalence of these two agents, this trial will also test two different treatment regimes. The process to establish the daily dose and length of treatment for BZN and NFX (two agents developed since the 1960s) did not undergo rigorous evaluation. Recent reports on pharmacokinetics of BZN in children have suggested that under the recommended daily dose for adults (5 mg/kg a day) blood levels would exceed by twofold those with a proven trypanocidal effect for children [21]. If that is the case, and side effects are dose-related, halving the dose may promote tolerance. Conversely, another study in adults has suggested that serum levels of BZN are not associated with side effects [22]. Other authors have suggested that the length of exposure (i.e. cumulative doses) is what may trigger intolerance to BZN [23]. Others have, in fact, started tests of shorter, intermittent treatments with BZN [24]. Guidelines for treatment of *T. cruzi* infection indeed vary in the dose, but also in the length of therapy, mainly between 60 and 90 days [25]. Through comparison of the 60CD and 120HD treatment schemes, our study will inform whether tolerance to nitro derivatives NFX or BZN treatment is associated with doses or exposure.

EQUITY has some limitations. Firstly, its primary efficacy outcome is parasite-related. Establishing an effective regime that is well tolerated is an intermediate, necessary step for future testing of its clinical impact. In fact, in the placebo-controlled BENEFIT trial (where 20% of the population did not respond to BZN and 13% abandoned their treatment), the clinical impact went consistently towards benefit, but without statistically significant effect (7% reduction in its primary outcome, a composite of cardiac complications or death) [11]. Thus, choice of a treatment scheme with a better efficacy/tolerance ratio would be critical to identify a potential clinical impact. Secondly, as the trial relies on limited resources, it will have a limited geographical variety in its population. By having Colombia as the main participating country, we will address two needs: to run a new trial testing NFX (the first in Colombia, where a previous quasi-experiment showed positive results [26]), and to replicate (or challenge) previous results of the BENEFIT trial showing no trypanocidal effect. Thirdly, our study will test a limited amount of possibilities for trypanocidal therapy. The EQUITY trial will focus on the foundations to use NFX and to recommend it as an equivalent of BZN. Keeping the trial within this reach allows statistical power for the two main questions, at a cost of leaving, for example, combinations, other treatment schemes and other agents untested.

Finally, conducting a trial like EQUITY will, for the local capacity, provide a useful and constructive experience. This trial will increase much-needed clinical trial data on *T. cruzi*-infected populations from Andean countries. In that regard, EQUITY will join two recent trials including Bolivian patients or immigrants living in Spain [12, 13]. Investigator-initiated trials originating from Colombia are still scarce, and are a challenge for promotion among funding and regulatory agencies as well as research departments and laboratories. For this and other neglected tropical diseases, this type of trials may also be seen as a responsibility for endemic countries.

### Trial status

The Protocol Version is 2.0, dated 6 November 2015. The EQUITY trial obtained external funding (call 569, 2012) from Colciencias in February 2014. After obtaining institutional approvals, receiving raw study drugs from the ministry of health, re-packing the study medication and building the randomisation system, recruitment started on October 2015 in Colombia. Recruitment in additional countries started in June 2018 in Argentina. EQUITY is actively seeking up to three additional centres in southern cone countries. We will keep recruitment open outside Colombia up to having 500 participants or until the end of June 2019, whichever comes first. Last follow-up and database closure are expected by the end of 2020, and final results are planned to be reported by May 2021.

## Data Availability

Any data and materials supporting information of this article can be requested from the corresponding author.

## Abbreviations

ALAT: Alanine amino transferase
ASAT: Aspartate amino transferase
BID: Twice a day
BZN: Benznidazole
CD: Conventional dose
EDTA: Ethylenediaminetetraacetic acid
HD: Half dose
NFX: Nifurtimox
PCR: Polymerase chain reaction
TC +: *T. cruzi* positive serology
